### Assessments

The following assessments will be carried out during the project, cf. Fig. 1. Details of the low- and high-intensity interventions are described in the “Interventions” section.

**Fig. 1 Fig1:**
[figure not shown]
SPIRIT figure: overview of assessments that each participant will undergo and the time schedule for the project

#### Smoking history

The age of smoking debut is obtained, the number of years smoked, the number of cigarettes/cigars/cheroots/grams of tobacco smoked, and the number of smoking cessation attempts in total, if they have tried to stop smoking within the last year and motivation for smoking cessation.

#### Blood tests

The following are the standard blood samples: electrolyte parameters (sodium, potassium), kidney parameters (creatinine, carbamide), liver parameters (albumin, bilirubin, ALAT, alkalic phosphatase, INR), CRP, glucose, HbA1c, hematologic differential blood cell count, and hemoglobin and iron content.

#### Questionnaires

Standardized questionnaires are used. CAT and MRC dyspnea scale are short and simple tests that provide an understanding of the severity and impact of COPD on the participant’s daily life. HADS is used to screen for anxiety and depression, and HAM-D is used to suggest a risk of developing depression.

### Scientific ethics statement

The study is performed according to the Helsinki Declaration and is carried out in accordance with the rules in the Personal Data Act and the Health Act. Approval will be sought from the Danish Data Protection Agency. Recruitment and inclusion will take place as previously described. Participation requires a signed informed consent statement. Participants can withdraw their consent at any time and withdraw from the research project without affecting their right to current or future treatment. Participants who do not wish to participate in the trial will be offered treatment according to current guidelines. The participant also has the right to bring an advisor to the information conversation and is entitled to a reflection period before any consent form is signed. If, during the experiment, significant information emerges about the individual’s state of health, this will be disclosed both in written and orally to the participant, unless he or she has refused to do so in advance in the signed consent statement.

### Data collection

The primary daily project management is handled by the project manager. In addition, a project group (investigators), consisting of health professionals from the departments involved, is trained to assist the project manager with the recruitment, sampling, and follow-up of participants. Recruitment in general practice is done by the project-trained nurse. Assignments for project staff after patient allocation are detailed in standard operating procedures (SOPs), depending on the allocation to intervention or control group.

Upon entering the program and all visits in the future (after 1, 3, 6, 12, 24, and 36 months), the participant is summoned to a conversation with staff, asking if the participant smokes (yes vs. no), and if yes, how much. In addition, a urine sample is taken with cotinine analysis for biochemical verification of smoking status and standard blood samples to examine health status at these visits (analyzed on the Department of Clinical Biochemistry, KBA). In addition, questionnaires (CAT, MRC, and HADS) are completed with the participant.

In the case of inclusion and follow-up visits after 3, 6, 12, 24, and 36 months, lung function measurement is also carried out at regular intervals by spirometry. Smoking anamnesis and height measurement are done by inclusion in the study along with weight measurement, which is only further measured after 6, 12, 24, and 36 months to monitor BMI.

The HAM-D score is measured at inclusion, and again after 12, 24, and 36 months, and if the score becomes high (≥ 25), i.e., that there is a high risk of developing depression, the participant will be advised to see their GP for further evaluation.

In addition, sputum samples are induced for microbiome analysis at the time of inclusion into the study, and again after 12 months in the first 50 participants in the “high-intensity” group who quit smoking and in the first 50 participants in the “low-intensity” group who do not quit smoking.

Confirmation of death (including the cause of death) is obtained from the Cause of Death Register (DAR). Admissions, hospitalization, and the participant’s diagnoses are retrieved from their records. Comorbidities and prescribed therapy and filled prescriptions are recorded at inclusion and on an ongoing basis during study visits. During the trial, the following are also recorded: side effects and analyses from the paraclinical tests. At the same time, it is also stated that varenicline does not cause critical interactions with other drugs (see www.interaktionsdatabasen.dk and product summary).

Collected data will be treated confidentially by the staff associated with the project. Data will be reported in electronic case report forms (eCRF) specific to each participant, which are encrypted and stored in servers protected by Danish data security authorities with double login to REDCap (with automatic range checks during data entry to prevent unrealistic data entries). In addition to the above information, the following data are recorded by inclusion: demographic data, health status, current and previous drug consumption, current and past diseases. Physical copies of CRF are kept in locked archives for the departments involved for 15 years. A Good Clinical Practice (GCP) coordinator, independent from investigators and the sponsor, will continuously monitor the trial and ensure that recruitment, data entry, etc. have been done correctly.

### Information from patient journals

Information from the trial participants’ journals is obtained under the study to obtain study-relevant information (information to be used for the study-specific case report form or corresponding to the data to be obtained for subsequently approved additional protocols). If informed consent is obtained from the trial participants, it is permissible for the investigators to obtain this information from the patient record. Study-relevant information includes data on COPD severity, risk profile, disease development, and relevant co-morbidity to answer the hypothesis described. The informed consent also gives investigators, COP:TRIN, their representatives, and eventual monitoring authority direct access to obtain information in the participant’s journal, etc., including electronic journal, in order to see information about the participant’s health conditions, which are necessary in order to complete the research project and in monitoring purposes, including self-monitoring and quality monitoring, as these are required to be performed. No information from patient records is obtained until informed consent has been obtained from participants.

### Remuneration/services

No remuneration is paid to the study participants.

### Biological material

Blood samples are taken by venipuncture, and throughout the study period of up to 36 months, the blood drawn will be up to 120 ml of blood (a maximum of 18 ml per visit).

The collection of induced sputum will be done by mask inhalation with hypertonic saline solution [18]. Participants are thoroughly instructed by a respiratory nurse to expectorate into a container. Samples are frozen in − 80 °C freezer within 24 h.

### Research biobank

A research biobank is created for storing blood samples, urine samples, and sputum samples. In total, up to 120 ml of blood will be taken from each participant from inclusion to 36 months of follow-up. All samples are stored in a freezer in a locked room for analysis before the project ends. Microbiome analyses are performed on the sputum samples at Statens Serum Institut or another laboratory that has recognized expertise in microbiome analysis. All samples are kept in a pseudoanonymized form for 15 years, where they are analyzed and will be done in the years after recruitment is completed. This research biobank will be used to answer the hypotheses described in this protocol, including sub-studies. The research biobank ends at the end of the recruitment process, and all surplus material is transferred to a biobank for future research (see below). The analyses consist of standard blood sample analyses to check health status: electrolyte parameters (sodium, potassium), kidney parameters (creatinine, carbamide), liver parameters (albumin, bilirubin, ALAT, alkalic phosphatase, INR), CRP, glucose, HbA1c, hematologic differential blood cell count, and hemoglobin and iron content. Additionally, at inclusion, cotinine is analyzed in the blood for immediate analysis, and all excess material is transferred to the research biobank. The urine sample is analyzed for cotinine content for biochemical smoking status, and the sputum samples are examined for the microorganism composition (microbiome analysis).

#### Biobank for future research

Permission to create a new biobank for future research with the excess material will be sought from The Danish Data Protection Agency. Following the end of the project and the research biobank, the excess material will be transferred to this new biobank for future research within the COPD disease. The samples (the excess material from the research biobank) will be locked away and stored pseudoanonymized for 15 years in accordance with the current legislation including data protection laws. Informed consent to participate in the project permits biological material to be stored in the research biobank and the excess material in the biobank for future research.

### Risks, adverse effects, and events

When taking blood samples, transient discoloration of the puncture site is observed frequently (in 5–15%) due to a minor blood accumulation under the skin (bruising). In addition, there is a risk of slight pain during the insertion of the needle and minimal risk of infection.

There are no known risks and side effects associated with urine and sputum collection.

It is a general rule that all effective medications can also have side effects. For varenicline, mild nausea and abnormal dreams are the most common side effects. A complete list of all known adverse effects with varenicline is found at https://pro.medicin.dk/Medicin/Praeparater/4063.

It should be said that smoking cessation itself can give rise to several symptoms, and it may be difficult to distinguish between these symptoms and the side effects of the treatment. The summary of product characteristics of varenicline is used as a reference document when assessing whether a serious adverse reaction (SAR) is expected/unexpected and thus may be a suspected unexpected serious adverse reaction (SUSAR).

The investigator must report all serious incidents/side effects (SAR) to the sponsor as soon as possible. Thus, the sponsor can immediately report on to the Danish Medicines Agency and the Danish Committee on Health Research Ethics if it is deemed to be a SUSAR. In case of fatal or life-threatening side effects, this must be recorded and reported to the National Board of Health within 7 days of the sponsor being aware of such a suspected adverse reaction. Within 8 days of the report, the sponsor must notify the National Board of Health of all relevant information about the sponsor’s and investigator’s follow-up to the report. All other SUSARs must be reported to the Danish Medicines Agency no later than 15 days after the sponsor has gained knowledge of these. At the same time, test managers are informed at the other centers.

An annual list of all SUSARs that have occurred during the trial period is prepared and a report on the safety of the participants is submitted to the National Board of Health. In addition, all adverse reactions and events are reported at the end of the trial in the final report to the National Board of Health.

### Exclusion from or interruption of trial

If the physician responsible for the study considers it necessary, the person may at any time terminate the study if there is a medical justification (e.g., development of allergy to medication), a safety risk, or other circumstances. However, this must be done in agreement with the coordinating investigator. The participant may at any time, as mentioned in the above paragraph, withdraw their informed consent and withdraw from the project. It will not have any consequences for further treatment.

### Information about compensation schemes

The trial is covered by the patient compensation scheme if, contrary to expectation, damages occur during the trial and by inclusion.

#### Secondary endpoints

Number of admissions for exacerbations of COPD or death within 12 months (continuous)Number of admissions for all causes or death within 12 months (continuous)Number of cardiovascular events^1^ within 12 months (continuous)Changes in CAT score from baseline over 12 months (categorical)Changes in FEV_1_ from baseline over 12 months (continuous)Changes in BMI^2^ from baseline over 12 months (continuous)Clinically relevant changes in HADS score from baseline over 12 months (categorical, change in category 0–7, 8–10, and 11–21 points)Occurrence of DNA from the following: *M. catarrhalis*, *H. influenzae*, and *P. aeruginosa* over 12 months^3^ (dichotomous, measured as change in test result from baseline)Changes in the total lung microbiome over 12 months^3^ (continuous, measured as change in the total composition of lung microbiome from baseline)Occurrence of smoking-related cancer^4^ within 12 months (dichotomous)Number of admissions requiring NIV treatment or admissions to intensive care or death within 12 months (continuous)Changes in status from MRC dyspnea score from < 3 to ≥ 3, over 12 months (dichotomous)

^1^Defined as cardiovascular death, acute myocardial infarction, or unstable angina pectoris [19].

^2^BMI loss more than 1 unit.

^3^These endpoints are only examined on the first 50 who stop smoking from the “high-intensity” group against the first 50 who do not stop smoking from the “low-intensity” group.

^4^Lung cancer, urothelial cancer, pancreatic cancer, esophageal cancer, pharyngeal cancer, laryngeal cancer, tongue cancer, oral cancer, and tonsil cancer.

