#### Long-term (follow-up) endpoints

Occurrence of depression within 36 months (dichotomous)
Admission to psychiatry with depression as the primary diagnosis (dichotomous)New start of antidepressant treatment after baseline (dichotomous)Clinically relevant changes in HADS score over 36 months (categorical)Changes in status from HAM-D score from baseline over 36 months (categorical, change in category 13–17, 18–24, and 25–52 points)Number of days during antidepressant treatment from baseline over 36 months (continuous)Changes in FEV_1_ from baseline over 36 months (continuous)

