### Analyses

Data will be analyzed (blinded) using intention-to-treat (ITT) principles, including all the data available, regardless of whether the intervention was completed or not. The aims of the ITT analysis are also to provide unbiased comparisons among the two study groups and to avoid the effects of potential study dropouts and protocol deviations. Patients in the intervention group will be compared to patients in the control group.

For the primary outcome, the percentage of patients who have ceased smoking in each group will be calculated and the two groups will be compared using logistic regression. For the dichotomous outcomes and the nominal outcomes, both presented as counts and percentages, Fisher’s exact test and chi-squared test will be used, and the timed dichotomous outcomes will be visualized through Kaplan-Meier plots. In addition, the ordinal outcomes (also presented as counts and percentages) will be analyzed with the Mann-Whitney *U* test. Continuous outcomes will be expressed as means, standard deviations, and interquartile ranges and will be analyzed with *t* tests if normally distributed and Mann-Whitney *U* tests if non-normally distributed. Furthermore, adjusted analyses will be performed with a multivariable Cox proportional hazards model, adjusting for baseline variables and calculating hazard ratio. In addition, the combined outcomes “number of admissions for exacerbations of COPD or death …” and “number of admissions for all causes or death …” will be analyzed in a generalized linear model. Data will be processed and analyzed in SAS with graphs generated therein and in other graph programs such as SPSS.

A Data Safety Monitoring Board, independent from sponsor and competing interests, will monitor the safety of the trial by conducting interim analyzes based on primary and secondary endpoints when half of the study population has completed the study, and thus recommend continuation or termination of the trial.

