### Sample size (statistical power calculation)

Type 1 error limit (*α*) of 5%. Power (1-*β*) of 90%.

The maximum smoking cessation rate for the “low-intensity group” is expected to be 10% in 12 months. With the above-described person-adapted, multi-component, intensive smoking cessation intervention in the “high-intensity group”, ≥ 20% of participants are expected to cease tobacco smoking for at least 12 months. Thus, a 10% absolute improvement in the likelihood of smoking cessation is expected, in this case, equivalent to the relative risk of smoking cessation on 2.0. This gives a sample size of 532 (266 + 266) persons. To account for possible withdrawal from the study and lost to follow-up, 600 participants will be recruited for the project.

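### The HADS endpoint treats any band crossing as a clinically relevant change and has no analysis of the score itself, which costs precision and makes the label misleading

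*Protocol article*

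**What the plan says.** The secondary endpoint list has "Clinically relevant changes in HADS score from baseline over 12 months (categorical, change in category 0–7, 8–10, and 11–21 points". The long-term list repeats the label as "Clinically relevant changes in HADS score over 36 months (categorical" and does not restate the bands; I read it as using the same ones. Under Questionnaires, the article says that "HADS is used to screen for anxiety and depression". Under Data collection, at entry and at the visits after 1, 3, 6, 12, 24 and 36 months, "questionnaires (CAT, MRC, and HADS) are completed with the participant", so the numeric score exists at baseline and at both analysis times.

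The Analyses section handles categorical outcomes in two ways: "For the dichotomous outcomes and the nominal outcomes, both presented as counts and percentages, Fisher’s exact test and chi-squared test will be used", and "the ordinal outcomes (also presented as counts and percentages) will be analyzed with the Mann-Whitney *U* test". It gives t tests or Mann-Whitney tests for continuous outcomes, but HADS is labelled categorical, whereas the changes in FEV1 and BMI are labelled continuous. No analysis of the HADS score as a number is listed.

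**The concern.** Screening bands classify a person's status at one visit. They do not say how large a change between two visits must be to matter. The endpoint uses them for that second purpose and calls every crossing clinically relevant. Two things follow. The reported percentage will include small moves near a cut and leave out large moves within a band. And reducing a 0–21 score to three bands discards information, so a real difference in mood between the arms is more likely to be missed. HADS supports a secondary endpoint and, through its questionnaires, the depression and anxiety sub-study, so a diluted null result could be read as evidence of no mood effect.

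**Working it through.** **1. The plan's own power figure.** The only one is for the primary endpoint: 10% against 20%, alpha 5%, power 90%. Two-sided, with pooled variance:

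n per arm = [1.96·√(2·0.15·0.85) + 1.2816·√(0.10·0.90 + 0.20·0.80)]² / 0.10² = (0.990 + 0.641)² / 0.01 = 265.9, so 266 per arm and 532 in total.

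This matches the article. It does not depend on HADS; 266 per arm is used below only as the number analysed.

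**2. The band rule (exact, no assumptions).** Of the 21 one-point upward steps on 0–21, two cross a band.

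| Move | Points | Counted? |
|---|---|---|
| 7 to 8 | 1 | yes |
| 10 to 11 | 1 | yes |
| 8 to 10 | 2 | no |
| 0 to 7 | 7 | no |
| 11 to 21 | 10 | no |

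**3. Band changes with no true change (assumed inputs).** The documents give no HADS mean, SD or reliability. Assumed: gamma-distributed true score with mean 4.5–6 and SD 3.5–4; independent normal error with SD 1–2 at each visit; scores rounded and clipped to 0–21; 400,000 records per setting.

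- Changing band: about 8% (mean 4.5, SD 4, error SD 1) to about 25% (mean 6, SD 3.5, error SD 2), half in each direction.
- Among those observed at 8–10 at baseline: about 38–65%.
- Share of these changes that are moves of at most 2 points: about a third to 77%.

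A wider set (normal scores, mean 4–8, SD 3–4, reliability 0.7–0.9) gives 8.5–40%. The proportion would be lower if baseline scores lay far below 8.

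**4. Power, 266 per arm (assumed inputs).** Mean 6, true SD 4, error SD 1.5, within-person SD of true change 2, two-sided 5%.

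Closed-form check for the baseline-adjusted score with a 1-point difference, ignoring rounding and clipping:
- baseline variance = 16 + 2.25 = 18.25
- follow-up variance = 16 + 4 + 2.25 = 22.25
- covariance = 16
- residual variance = 22.25 − 16²/18.25 = 8.22, so residual SD = 2.87
- SE = 2.87·√(2/266) = 0.249
- power = Φ(1/0.249 − 1.96) = Φ(2.06) = 0.98

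Simulation with rounding and clipping (1,500 trials per setting):

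| True difference | Mann-Whitney on signed band shift | Baseline-adjusted score |
|---|---|---|
| 1-point improvement | about 60% | about 97% |
| 1-point worsening | 68–76%, depending on simulation details | about 98% |
| 1.5-point improvement | about 87% | about 100% |
| 2 points, either direction | 98% or more | about 100% |

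With no true difference, both analyses reject in about 5% of trials.

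**The case against.** The strongest defence is that a band shift suits a screening instrument. If the question is who moves into or out of a screening category, then 0 to 7 is rightly no shift, and a three-band outcome is legitimate. That stands for a band shift named as such. It does not justify the words clinically relevant, and it gives no reason to leave the score unanalysed.

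A reader might go further and infer that improvement and worsening are pooled into changed against unchanged. In the setting above that would leave about 8–9% power for a 1-point improvement. The article does not say this. It calls the endpoint categorical, while it uses dichotomous for others in the same list; the bands are ordered; and ordinal outcomes go to the Mann-Whitney test, which keeps the two directions apart. The fair comparison is therefore the signed shift against the score.

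A reader might also infer a biased comparison. Measurement noise alone gives none: it should be alike in both arms when there is no effect, and the error rate stays near 5%.

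The noise and power figures do rest on assumed inputs, and the article states no expected HADS effect. Confirmation of a change and a minimum-point responder threshold are details that an analysis plan may settle, and any such threshold has its own cut-point problem; neither is part of this point. The score analysis could also appear in an analysis plan not shown, but the protocol fixes the endpoint as categorical, and a plan that follows it would inherit that.

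**Conclusion.** The point holds as one of labelling and efficiency. That one-point crossings count and moves of up to 10 points do not follows directly from the printed bands. The size of the loss is conditional: with the assumed inputs, about 8–25% of participants change band with no true change, and power for a 1-point difference is about 60–76% on signed band shift against about 97% on the adjusted score. The loss is largest for effects of about 1 point and small from 2 points upwards. It touches one of twelve secondary endpoints and its 36-month repeat. The primary endpoint and the sample size of 532 are not affected.

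**What to change.** Make the HADS analysis at 12 and at 36 months a linear regression of the score on arm, with baseline HADS as covariate. Keep the table of band shifts as description, with worsening and improvement shown separately, and name it change in HADS category instead of clinically relevant change. State at 36 months that the same bands apply.

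The cost is wording only, since the score is already collected at baseline and at every follow-up visit. The downside is that the category percentages become descriptive and no longer carry the test.

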## Methods

### Design

This is a randomized open-label, superiority, multicenter, 2-arm intervention study, in which it is examined if a “high-intensity” intervention causes fewer people (diagnosed with COPD) to smoke after 12 months than in a “low-intensity” intervention in people diagnosed with COPD. The effect on survival for 12, 24, and 48 months; incidence of COPD exacerbations; number of admissions for all causes; and cardiovascular admissions will also be analyzed at the same time.

Additionally, a few sub-studies will be conducted:
Sub-study 1: We will examine the prevalence of depression/anxiety within 36 months in the “high-intensity” and “low-intensity” groups by means of questionnaires, by hospital admissions, and by recording the prescription of drugs for depression and anxiety.Sub-study 2: In a subset of patients who quit smoking from the “high-intensity” group (*n* = 50) and patients who do not quit smoking from the “low-intensity” group (*n* = 50), we are going to examine the potential changes in the respiratory microbiome within 6 months of smoking cessation attempt.

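### The two microbiome secondary endpoints set high-intensity quitters against low-intensity non-quitters, so quitting and trial arm cannot be separated, enrolment period is strongly imbalanced, and follow-up is given as both 6 and 12 months

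*Protocol article*

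**What the plan says.** Three places in the protocol article define the microbiome comparison.

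- **Secondary endpoints, footnote 3** covers the DNA of three named bacteria and the total lung microbiome. It admits only the earliest 50 quitters of the high-intensity arm, who are set "against the first 50 who do not stop smoking from the" low-intensity arm. The second of these endpoints reads "Changes in the total lung microbiome over 12 months".
- **Data collection** repeats the selection and gives the sampling times: "sputum samples are induced for microbiome analysis at the time of inclusion into the study, and again after 12 months". This later sample is limited to the same two groups, quitters in one arm and non-quitters in the other.
- **Design, Sub-study 2** describes the same cross-arm groups, 50 in each, but the aim is to "examine the potential changes in the respiratory microbiome within 6 months of smoking cessation attempt".

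The Analyses section says that the trial's data are analysed by intention to treat, with the intervention arm set against the control arm, and gives unbiased comparison of the two arms as an aim. It makes no exception for the two microbiome endpoints.

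**The concern.** The endpoints stand in the list of secondary endpoints of a randomised trial, but the groups compared are not the randomised groups. Each is picked on what happened after randomisation, in opposite directions in the two arms. A difference in microbiome change could come from any of these sources:

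- stopping smoking;
- the rest of the high-intensity programme, such as the physiotherapist's training, the dietician's advice and the buddy arrangement;
- the kind of person who manages to quit;
- the period in which the person was enrolled, because quitters are expected to be scarce and non-quitters plentiful, so the earliest 50 of each build up at very different speeds.

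At stake is whether a finding on these endpoints can be read as an effect of cessation, or of the intervention. In addition, the objective and the sampling schedule give different time windows, so the Sub-study 2 objective cannot be met with the samples described.

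**Working it through.** **1. Which combinations are sampled.** Crossing arm with quit status gives four cells:

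| | Quit | Did not quit |
|---|---|---|
| High-intensity | 50 | none |
| Low-intensity | none | 50 |

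Every quitter is in the high-intensity arm and every non-quitter is in the low-intensity arm. Arm and quit status are therefore the same variable in this sample. No adjustment can separate them, and no analysis plan could repair this afterwards, because the two empty cells have no 12-month sputum.

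**2. The planning rates.** The Sample size section gives quit rates of at most 10% (low-intensity) and at least 20% (high-intensity), with alpha 5% and power 90%. The usual two-sided formula without continuity correction is

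n per arm = [1.960 × √(2 × 0.15 × 0.85) + 1.2816 × √(0.10 × 0.90 + 0.20 × 0.80)]² / 0.10² = (0.990 + 0.641)² / 0.01 ≈ 266.

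This reproduces the stated 266 + 266 = 532, so 10% and 20% are the rates that the plan works with. The article gives no calculation for the 50 versus 50 comparison.

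**3. How far into each arm the selection reaches.** Participants needed = 50 / (probability of the selecting outcome). Months = participants needed / 300 × 36. The 300 per arm is half of the 600 to be recruited, and the 36 months run from 1 January 2020 to 1 January 2023 (Trial status). Even accrual, and selection in enrolment order on 12-month quit status, are assumptions; the article states neither.

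| Group | Assumed quit rate | Participants needed | Months |
|---|---|---|---|
| Low-intensity non-quitters | 5% | 50/0.95 ≈ 53 | 6.3 |
| | 10% (plan) | 50/0.90 ≈ 56 | 6.7 |
| | 20% | 50/0.80 ≈ 63 | 7.5 |
| High-intensity quitters | 30% | 50/0.30 ≈ 167 | 20 |
| | 20% (plan) | 50/0.20 = 250 | 30 |
| | 15% | 50/0.15 ≈ 333 | more than the 300 in the arm |

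**4. Overlap in enrolment period.** At the planning rates, the window that supplies the non-quitters covers about the first 56 participants of each arm. The high-intensity arm should yield about 56 × 0.20 ≈ 11 quitters in that window, so about 11 of the 50 quitters are contemporaries of the non-quitters and about 39 come later.

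**5. Supply of quitters.** At exactly 20%, 0.20 × 300 = 60 quitters are expected, so 50/60 = 83% of them must give paired sputum. If only 266 were evaluable, 0.20 × 266 ≈ 53 are expected and the share is 50/53 ≈ 94%. The article does not call 266 an evaluable count, so the second figure is a scenario only. The high-intensity arm should also contain about 300 − 60 = 240 non-quitters.

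**6. Follow-up time.** Design: "changes in the respiratory microbiome within 6 months of smoking cessation attempt". Data collection: sputum at inclusion and after 12 months. Secondary endpoints: over 12 months. Data collection does list a 6-month visit, but schedules no sputum there.

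**The case against.** The strongest defence is that the restriction is open and deliberate. The Design section calls this a sub-study in a subset chosen by quit status and promises only to look at potential changes. Footnote 3 can be read as a specific exception to the general intention-to-treat sentence. Opposite extremes also give a sharp smoking contrast. Part of this stands: the article does not claim in so many words that the microbiome comparison is an unbiased randomised effect, and the primary comparison is untouched. But the two endpoints are listed with the other secondary endpoints, and the Analyses section does not set them apart. Nor does the contrast need two arms, since the high-intensity arm alone should supply both quitters and non-quitters.

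A reader might infer that enrolment period, too, is fully confounded with group. The documents do not support that. The span that yields the quitters includes the early window that yields the non-quitters, and about 11 of the 50 quitters are expected from it. The month figures also rest on even accrual and on a reading of selection order that the article does not give. The planned 20% is a minimum, and a higher quit rate shortens the gap. Both endpoints are changes from the person's own baseline, and samples are frozen and apparently analysed after recruitment, which makes assay drift by enrolment date less likely. Calendar period is therefore a secondary weakness.

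Weekly calls are not a safe example of an arm difference: they are listed under the high-intensity arm but worded as going to everyone in the project. The argument does not need them.

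It is also fair to say that comparing quitters with non-quitters within one arm remains a comparison of self-selected people. That limits what the remedy achieves, but the remedy does remove the arm.

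**Conclusion.** The point holds for the two microbiome endpoints. Quitting and trial arm are fully confounded, the groups are formed on a post-randomisation outcome, and the result is not an intention-to-treat comparison of the arms. As planned, a difference can be attributed neither to cessation nor to the programme. This follows from the text alone and needs no assumption.

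Enrolment period is strongly imbalanced but overlapping: about 6 to 8 months of accrual for the non-quitters, against about 20 to 30 months for the quitters at quit rates of 30% down to 20%. At 15% the high-intensity arm is expected to fall short of 50 quitters. These figures assume even accrual of 300 per arm over 36 months and selection in enrolment order on 12-month status.

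Separately, the 6-month window in the Design section contradicts the 12-month sampling and endpoints, and no 6-month sputum sample is described that could serve it.

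**What to change.** 1. **Label.** Describe both microbiome endpoints as an observational sub-study, outside the randomised, intention-to-treat secondary comparisons. This is a wording change.
2. **Time.** Reconcile the Design, Data collection and Secondary endpoints sections to one follow-up time that matches when sputum is taken.
3. **Comparison group.** Draw the 50 non-quitters from the high-intensity arm as well: for each quitter, the next enrolled non-quitter in the same stratification cell (age group by daily cigarettes). Analyse change by quit status, adjusted for the baseline sample, age and cigarettes per day. This removes the arm as an explanation and most of the calendar imbalance.

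The cost is small. The number of paired samples stays at 100. Future quitters cannot be recognised at inclusion, so at the planned 20% rate baseline sputum is already needed from about 250 high-intensity participants. The price is that there is no low-intensity sputum, and that quitters and non-quitters still differ in ways that adjustment may not capture; the protocol should say so.

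If the sponsor prefers to keep the cross-arm contrast, steps 1 and 2 still apply, and the protocol should state that the contrast cannot separate cessation from the programme.
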